## Abstract

Patients with Parkinson's disease (PD) have difficulties while performing dual-task activities, a condition present in everyday life. It is possible that strategies such as transcranial Direct Current Stimulation (tDCS) can be associated with motor training enriched with dual-task training to improve the performance of two concurrent tasks. Currently, it is unclear whether specific tasks and clinical conditions of PD patients have different results after the intervention. Therefore, the proposed randomized controlled trial will examine task-dependency in enhancing the effects of tDCS-linked rehabilitation training on PD and the relationships between baseline outcomes in responders and non-responders to therapy. Fifty-six patients with Parkinson's disease will be recruited to participate in this controlled, double-blind randomized multicentric clinical trial. Patients in modified Hoehn & Yahr stage 1.5–3, age between 40 and 70 years will be included. Subjects will be randomly assigned to an experimental group (EG) and a control group (CG). The EG will perform treadmill gait training associated with dual task exercises+tDCS, while the CG will only engage in treadmill gait training+tDCS. Blinded testers will assess patients before and after 12 intervention sessions and after a 4-week follow-up period. All patients will undergo a screening and an initial visit before being assessed for primary and secondary outcomes. The primary outcome measure is functional mobility measured by Timed Up and Go Test. Secondary outcomes include cognitive function, participation, motor function and body function and structure. This study will evaluate the effectiveness of an intervention protocol with tDCS, dual-task training and gait training in patients with PD. The study will also highlight the clinical factors and variability between individuals that could interfere in the training of a specific task and influence the therapeutic effect.

**Clinical Trial registration**: www.ClinicalTrials.gov, identifier NCT04581590.

## 1. Introduction

Parkinson's disease (PD) is a neurodegenerative disorder that affects motor and cognitive function, especially when individuals are submitted to dual tasks (Cameron et al., 2010; Kelly et al., 2012). During concomitant cognitive and motor tasks, the cerebral cortex prioritizes cognition, which may increase the risk of falls (Yarnall et al., 2011) and, consequently, of fractures and trauma (Duncan et al., 2011).

In PD, progressive cognitive impairment related to executive function, memory oscillation, language and visuospatial capacity may be present in the initial stages of the disease (Yarnall et al., 2014). Executive dysfunction occurs in 20% to 70% of cases (Elgh et al., 2009) and can help predict the occurrence of dementia in PD (Anang et al., 2014), with dysfunction in cognitive flexibility and operational memory (Domellöf et al., 2011) becoming more pronounced as the disease progresses (Ebersbach et al., 2013).

According to Vervoort et al. (2016), when compared to healthy individuals, those with PD exhibit changes in the brain connectivity of motor areas and the cerebellum when a dual task is required. Given the difficulty in executive function that these individuals face, dual-task training is recommended for this population (Brauer and Morris, 2010; Strouwen et al., 2014; Geroin et al., 2018). In addition, evidence shows the benefit of combined therapies to treat the disease (Zhou et al., 2014; Manenti et al., 2016; Vervoort et al., 2016), demonstrating improvement when patients with PD are submitted to cognitive training during gait while performing a dual task (Yogev-Seligmann et al., 2012). Among the non-pharmacological therapies is the association between transcranial direct current stimulation (tDCS) and rehabilitation protocols (Manenti et al., 2018; Beretta et al., 2020). It is suggested that synergic effects occur when both therapies are applied simultaneously, due to a likely modulation of the circuits that control planning and execute motor tasks (Fregni et al., 2006; Benninger et al., 2010; Kaski et al., 2014), with possible neuroplastic changes in the feedback loops that regulate the cognitive components also affected by PD (Manor et al., 2018).

tDCS is used to modulate cortical excitability, due to its action on neural membrane potential, leading to neuronal hyperpolarization via cathodic stimulation or depolarization provided by anodic stimulation (Nitsche and Paulus, 2000). Several studies show that in the rehabilitation of people with PD, tDCS has positive effects on motor function (Fregni et al., 2006), gait and bradykinesia (Benninger et al., 2010). When combined with physical training, tDCS can improve speed and balance during locomotion (Kaski et al., 2014) and seems to prolong the effects of motor intervention (Costa-Ribeiro et al., 2017).

Despite the promising results in reducing the symptoms of PD, the predictive factors that lead to a better response to intervention remain largely unknown. Disease severity, the medication dose in use, clinical type and freezing of gait seem to influence the effect and response to therapy. In relation to individual vulnerability, it is still unclear for whom these benefits apply, that is, whether age, disease severity or even emotional aspects linked to depression and anxiety before treatment determine treatment responsiveness (Carrarini et al., 2019). Moreover, the heterogeneity of the protocols used in the studies reflect the lack of understanding task-dependency associated with tDCS (Schoellmann et al., 2019). Which motor and cognitive components should be emphasized during tDCS-linked training has been little studied and whether multimodal protocols with mixed training should be prioritized over strictly motor or cognitive tasks.

In this clinical trial, we sought to investigate two aspects. First, to examine task-dependency in enhancing the effects of tDCS-linked rehabilitation training on PD. The relationships between baseline outcomes in responders and non-responders to therapy will also be examined, once, we also hypothesize that differences in clinical variables such as disease severity and depression symptoms may affect treatment effectiveness. In light of the evidence in previous studies (Swank et al., 2016; Manor et al., 2018), we hypothesize that a dual-task intervention program, including motor and cognitive paradigms, will be more robust in clinical measures than gait motor training alone.

## 2. Materials and Methods

### 2.1. Design

This is a controlled, double-blind randomized multicentric clinical trial, in line with the Standard Protocol Items Recommendations for Interventional Trials (SPIRIT) guideline (Chan, et al.), Figure 1. This project was approved by the Institutional Research Ethics Committee (30668420.7.0000.5188) and will be conducted according to the 1964 Declaration of Helsinki (Rickham, 1964). The trial was prospectively registered with the public platform clinical trials registry (www.clinicaltrials.org).

**Figure 1 F1:**
[figure not shown]
Schedule of enrollment, interventions and assessments demonstrated in the Standard Protocol Items: Recommendations for Interventional Trials (SPIRIT).

The treatment program for patients with PD will involve 12 sessions, three times a week. Study participants will be assessed at three different times: 4–7 days before the first intervention session, which will consider the baseline reference measure (T0); 4–7 days after the last session, considered a post-intervention measure (T1); and 30 days after the last intervention session, considered a post-intervention or follow-up measure (T2). Figure 2 illustrates the study design.

**Figure 2 F2:**
[figure not shown]
Design of the study. Legends: PD, Parkinson's disease, CG, Control Group, EG, Experimental Group, tDCS, transcranial direct current stimulation.

### 2.2. Participants

The following inclusion criteria will be applied: being diagnosed with idiopathic Parkinson's disease by a neurologist based on definitive evidence of responsiveness to levodopa at the start of the disease and the history of progressive hypokinesia with asymmetric onset. PD will be diagnosed based on Parkinson's Disease Society Brain Bank (PDSBB) criteria, as described in Hughes et al. (1992): age between 40 and 70 years, with no distinction for sex, schooling level or other sociodemographic characteristics; disease staging between 1.5 and 3, according to the modified Hoehn and Yahr scale (Hoehn and Yahr, 1998); undergoing regular pharmacological treatment with levodopa (equivalent dose > 300 mg) or taking antiparkinsonian medication, such as anticholinergics, selegiline, dopamine agonists, and COMT (catechol-O-methyl transferase) inhibitors for at least 4 weeks prior intervention; score of more than 24 points on the Mini-Mental State Examination (Folstein et al., 1975); not exhibiting other associated neurological diseases; and no musculoskeletal and/or cardiorespiratory changes that could compromise gait. The exclusion criteria will be diagnosis of atypical Parkinson's disease; neuropsychiatric comorbidities; convulsions, metal clips and/or pacemaker; deep brain stimulation implant; history of epilepsy; neurosurgery; traumatic brain injury; alcohol abuse or drug dependency; associated diseases of the peripheral or central nervous system; undergoing physical therapy at another location; inability to walk 10 meters; presence of important dyskinesia that prevents the participant from sitting in a chair; abnormal and persistent increase in systemic blood pressure before or during training, after three measurements taken 5 min apart-Cut-off: systolic blood pressure ≥ 140 mm Hg and/or diastolic ≥ 90 mm Hg (Malachias et al., 2016); not understanding any of the training protocol stages; chemical scalp treatment within the previous 30 days, and experiencing severe pain and/or discomfort that precludes performing the proposed activities.

History of falls in the last 12 months will be used to classify individuals into “non-fallers” (number of falls ≤ 1) or “recurrent fallers” (number of falls ≥ 2). Freezing of gait episodes will be screened and classified according to the dual-task screening questionnaire (Strouwen et al., 2014).

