### 2.3. Recruitment

The multicentric study will be conducted at several centers that have specific units or not, which provide specialized assistance to patients with PD. Participants will be recruited from hospitals and clinics, as well as social media and support groups. The records of subjects interested in taking part will be analyzed and included in the study if they meet the eligibility criteria. All the individuals that agree to participate will provide written informed consent.

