### 2.4. Randomization and Blinding

Participants will be randomly allocated, using an online generator (www.random.org), into two groups (1:1): CG) tDCS active + gait training; EG) tDCS active + gait training + dual-task. This sequence will be performed independently and remotely by a blinded investigator, who will have no knowledge of other study procedures. Randomization will be concealed until group allocation and stratified by subgroup with or without freezing of gait (FOG).

The concealed allocation process will be conducted using sequentially numbered sealed opaque envelopes. The outcome assessors, trialists and patients will be blinded to the procedures.

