#### 2.9.2. Rehabilitation Program

The participants will perform 12–20 min treadmill gait training associated to dual task exercises+tDCS, 3 times a week (Experimental Group) or treadmill gait training+tDCS (Control Group). If patients exhibit altered vital signs, they will be asked to remain seated and try to relax. If the situation persists, the patient will be instructed to visit their physician.

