### 2.10. Sample Calculation

The sample size power calculation was based on data from previous studies that used tDCS associated with motor training in people with PD (Manenti et al., 2016). The power calculations used to determine the number of participants in each group were made in relation to the expected change in functional mobility (primary outcome). Thus, a calculation considering *p* < 0.05 and 90% power as significant suggests that at least 46 patients would be necessary. Considering the possibility of sample losses throughout the study, we will aim to recruit 56 patients, totaling 28 participants per group.

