### 2.11. Data Analyses

The Statistical Package for the Social Sciences (SPSS), version 27.0, will be used in data analysis and a 5% alpha (*P* < 0.05) will be established.

The groups will be compared using the Student's *t*-test or Mann-Whitney test, for continuous variables, or the chi-squared test for categorical variables, according to the normality distribution, analyzed using the Shapiro-Wilk test. The primary outcome will be examined with a repeated measures split-plot ANOVA, with one dependent and two independent variables: one intragroup (time, with 3 levels: T0, T1 and T2), and one intergroup (a group with two levels: CG and EG) using Sidak's *post hoc* test. Analyses of covariance (ANCOVA) will be used to identify significant intergroup differences applying T0 scores as covariables. Linear regression will be used to identify response predictors. The independent variables will be group and clinical response, that is, the minimal clinically important difference (MCID). An intention to treat analysis will be conducted.

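### The blood-pressure exclusion criterion can be met during the randomised training, so as worded it permits exclusion after randomisation and sits badly with the intention-to-treat analysis

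*Protocol article*

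**What the plan says.** - **Section 2.2 (Participants).** The exclusion list includes "abnormal and persistent increase in systemic blood pressure before or during training, after three measurements taken 5 min apart", with the cut-off "systolic blood pressure ≥ 140 mm Hg and/or diastolic ≥ 90 mm Hg".
- **Section 2.3 (Recruitment).** Eligibility is applied at entry: "The records of subjects interested in taking part will be analyzed and included in the study if they meet the eligibility criteria".
- **Section 2.4 (Randomization and Blinding).** The arms are defined by the training they receive: "CG) tDCS active + gait training; EG) tDCS active + gait training + dual-task". Section 2.1 sets that programme at 12 sessions, three a week.
- **Section 2.9.2 (Rehabilitation Program).** A patient whose vital signs are altered sits and rests. Then: "If the situation persists, the patient will be instructed to visit their physician". Exclusion is not mentioned.
- **Section 2.11 (Data Analyses).** "An intention to treat analysis will be conducted".

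**The concern.** An exclusion criterion decides who enters a trial. Here one criterion can also be met by a patient who has been randomised and is on treatment, and the label attached to it is still exclusion. Intention to treat keeps every randomised patient in the assigned group, whatever happens on treatment.

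Section 2.9.2 gives a different instruction for an overlapping event, so staff have two texts to follow. Someone acting on section 2.2 could take the patient out of the study. Someone acting on sections 2.9.2 and 2.11 would pause training, refer the patient and keep the patient in.

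If patients were taken out, the Timed Up and Go comparison would rest on a set selected after randomisation by a measurement made under treatment. Randomisation no longer protects such a comparison.

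**Working it through.** The point turns on the text, so the main check is to read the sections in order of time.

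1. **Where the rule stands.** It is in the list of exclusion criteria (section 2.2), not among the attrition events (2.5) or the safety rules (2.8).
2. **When eligibility is decided.** At entry (section 2.3).
3. **When training happens.** The arms differ in their training (section 2.4), and the training is the 12-session programme (section 2.1). No training before allocation is described. A rise during training therefore comes after randomisation.
4. **Whether the rest of the criterion is anchored.** Before training could mean before enrolment or before each session. On the second reading, this part too can fall after allocation.
5. **Whether another section settles the matter.**
   - Section 2.5 counts absences, medication changes, missed evaluations and illness that prevents continuation as attrition. It does not name blood pressure.
   - Section 2.8 stops therapy for injury or strong discomfort, which is a different trigger.
   - Section 2.9.2 prescribes rest and referral. It neither mentions exclusion nor cancels section 2.2.
6. **What is said about analysis.** Section 2.11 states intention to treat. No section says that patients who meet the criterion during training leave T1, T2 or the analysis, and none says that they stay.

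**Scale, from the article's own numbers** (section 2.10: at least 46 needed, 56 recruited, 28 per group):

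- One patient excluded this way: 1/28 = 3.6% of an arm, or 1/56 = 1.8% of all randomised.
- Planned sessions at which the rule is open: 12 × 56 = 672. This counts opportunities and is not a measure of risk.
- Allowance for losses of every kind: 56 − 46 = 10, and 10/56 = 17.9%.

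**Power, for orientation only.** The 46 cannot be reproduced, because the article gives no effect size or standard deviation. Assume a two-sided 5% test of two means, 23 per arm and 90% power. The implied standardised difference is then (1.960 + 1.282) × √(2/23) ≈ 0.96. With that assumed effect, power falls as follows:

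| Share of the 56 lost, any cause (assumed) | Number analysed | Power |
|---|---|---|
| 0% | 56 | 94.7% |
| 10% | 50.4 | 92.4% |
| 17.9% | 46 | 90.0% |
| 25% | 42 | 87.2% |
| 30% | 39.2 | 84.9% |

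The share due to the blood-pressure rule cannot be derived. Precision is also the lesser issue: recruiting more patients does not repair selection after randomisation.

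**The case against.** The strongest reply is that the conflict is inferred. Section 2.2 governs who takes part and section 2.11 governs analysis. Both can be obeyed by stopping training for safety and analysing the patient as randomised, which is the ordinary case that intention to treat covers. Three readings 5 minutes apart look like a check around a single session. Section 2.9.2 is the only place that says what to do with altered vital signs in the programme, and it points to a safety action. Section 2.10 allows for losses ("Considering the possibility of sample losses throughout the study, we will aim to recruit 56 patients, totaling 28 participants per group"). Details of follow-up after stopping, and of the analysis set, commonly belong in a fuller protocol or analysis plan.

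Much of this stands. A reader might infer that the trial will drop these patients from the primary analysis, or that exclusion and analysis as randomised cannot coexist. The article supports neither inference. A reader might also infer that the dual-task arm would meet the rule more often, or that centres would act differently. Both are possible, but the article gives no evidence for either.

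The reply does not remove the wording problem. The article states the rule and calls it exclusion, so this is not a detail left to another document. If a safety stop is what is meant, the text should say so, and section 2.9.2 does not override the exclusion list.

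**Conclusion.** The point holds as a badly placed rule. Section 2.2 permits exclusion of randomised patients for an on-treatment blood-pressure event. That fits poorly with section 2.11 and differs from section 2.9.2. It should be corrected, because the correction is cheap and closes a route to exclusion after randomisation.

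The conclusion rests on two readings: that training means the randomised programme, and that no run-in precedes allocation. The article supports the first and describes nothing against the second.

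The size of any bias is unknown. It would depend on how often the rule is met, whether patients are in fact removed, and whether removal differs by arm. None of these is given.

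**What to change.** 1. In section 2.2, apply the blood-pressure exclusion only before randomisation, and delete the reference to a rise during training.
2. In section 2.9.2 or 2.8, make the same persistent finding after randomisation a reason to hold or stop the session, or training as a whole, with the physician referral already described.
3. State that these patients continue to the T1 and T2 assessments and are analysed in their randomised group.

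One option is not required by this fix. Section 2.1 counts the visits from the final session ("days after the last session, considered a post-intervention measure (T1"), which can be applied to a patient who stops early. Dating T1 and T2 from the planned 12th session instead would keep visit timing comparable, but that is a separate design choice.

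The cost is wording in two or three sections. The safety protection is unchanged. Some patients will be analysed with fewer than 12 sessions, which may slightly dilute the estimated effect.

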### 2.3. Recruitment

The multicentric study will be conducted at several centers that have specific units or not, which provide specialized assistance to patients with PD. Participants will be recruited from hospitals and clinics, as well as social media and support groups. The records of subjects interested in taking part will be analyzed and included in the study if they meet the eligibility criteria. All the individuals that agree to participate will provide written informed consent.

### 2.4. Randomization and Blinding

Participants will be randomly allocated, using an online generator (www.random.org), into two groups (1:1): CG) tDCS active + gait training; EG) tDCS active + gait training + dual-task. This sequence will be performed independently and remotely by a blinded investigator, who will have no knowledge of other study procedures. Randomization will be concealed until group allocation and stratified by subgroup with or without freezing of gait (FOG).

The concealed allocation process will be conducted using sequentially numbered sealed opaque envelopes. The outcome assessors, trialists and patients will be blinded to the procedures.

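### Allocation is stratified by freezing of gait but not by centre, and the models have no centre term: a modest, avoidable loss of balance and precision, not a bias

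*Protocol article*

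**What the plan says.** - Section 2.1 calls the trial multicentric. Section 2.3 adds that the centres are not alike: "The multicentric study will be conducted at several centers that have specific units or not, which provide specialized assistance to patients with PD".
- Section 2.4 allocates patients "into two groups (1:1" and names one stratification factor: "Randomization will be concealed until group allocation and stratified by subgroup with or without freezing of gait (FOG". Delivery is by envelope: "The concealed allocation process will be conducted using sequentially numbered sealed opaque envelopes". No centre stratum is named.
- Section 2.11 examines the primary outcome, the Timed Up and Go, with a split-plot ANOVA "with one dependent and two independent variables". These are "one intragroup (time, with 3 levels: T0, T1 and T2), and one intergroup (a group with two levels: CG and EG". The ANCOVA adds the T0 score as its covariate. Neither model lists centre, and neither lists freezing of gait, the factor used to stratify.
- Section 2.10 requires 46 patients for 90% power and plans to recruit 56, that is 28 per arm.

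**The concern.** The intervention is hands-on: treadmill training, verbal cueing and stepwise progression of task difficulty (Section 2.9). The primary outcome is a timed test (Section 2.7), administered by physicians and physiotherapists (Section 2.6). Centres may therefore differ in how much their patients improve, and not only in where they start. With centre left out of the allocation, one centre may by chance hold mostly EG patients and another mostly CG patients. With centre left out of the models, any centre difference in change then shifts the realised group comparison, and the remaining centre variance stays in the error term. With 23 to 28 patients per arm there is little room to absorb either effect. The allocation cannot be repaired after enrolment, and a centre term added once the data have been seen would be post hoc.

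**Working it through.** **Inputs from the protocol.** 56 patients recruited, 28:28; 46 evaluable, 23 per arm; alpha 0.05; power 90%. **Assumptions.** Two-sided test (sidedness is not stated); 3 to 6 centres of near-equal size; centre share of outcome variance 0, 10% or 20%.

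**1. The plan's own figure.** The 46 cannot be reproduced forward, because no effect size or SD is given. Solving backwards for 23 per arm, the normal approximation gives d = (1.960 + 1.282) × √(2/23) = 0.956, and the noncentral t gives d = 0.977. The second value is used in step 4.

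**2. Chance of a lopsided centre.** Treat allocation as a random 28:28 split that ignores centre. Call a centre lopsided if one arm holds at least 10/14 of its patients. Then

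P(some centre lopsided) = 1 − [Σ Π C(n_j, x_j)] / C(56, 28),

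where the sum runs over all sets of non-lopsided counts x_j that add to 28.

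| Centres | Sizes | Lopsided from | P |
|---|---|---|---|
| 3 | 19, 19, 18 | 14:5, 14:5, 13:5 | 7.6% |
| 4 | 14 each | 10:4 | 35.7% |
| 5 | 12, then 11 × 4 | 9:3, 8:3 | 54.2% |
| 6 | 10 × 2, 9 × 4 | 8:2, 7:2 | 50.9% |

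The small fall from 5 to 6 centres arises because centre sizes are whole numbers.

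**3. What that does to the estimate.** The centre-induced shift in the group difference is Σ w_j u_j, where w_j is the EG count minus the CG count in centre j, divided by 28, and u_j is the centre effect. Over random allocations E(Σ w_j²) = Σ n_j(56 − n_j) / (55 × 784).
- 3 centres: 2090/43120 = 0.0485, square root 0.220.
- 4 centres: 2352/43120 = 0.0545, square root 0.234.
- 6 centres: 2612/43120 = 0.0606, square root 0.246.

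Multiplying by √0.10 = 0.316 or √0.20 = 0.447, the SD of the shift runs from 0.220 × 0.316 = 0.07 to 0.246 × 0.447 = 0.11 outcome SD. The standard error of the comparison is about 0.28 to 0.29 SD, so the shift is real but small beside it.

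**4. Power.** Simulation with n = 46, d = 0.977 and a single outcome without T0 adjustment. There were 40,000 runs per cell, with blocks of 2 or 4 left incomplete where cells are small and 40% freezers assumed. The three columns are: as written (freezing strata, no centre term); centre-by-freezing strata with a centre term; and a centre term added to the allocation as written.

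| Centres | Centre share | As written | Both changed | Term only |
|---|---|---|---|---|
| 3 | 0 | 89.6% | 89.7% | 88.2% |
| 3 | 10% | 90.8% | 92.5% | 91.5% |
| 3 | 20% | 91.3% | 95.1% | 94.0% |
| 4 | 0 | 89.9% | 89.4% | 87.7% |
| 4 | 10% | 90.7% | 92.3% | 90.8% |
| 4 | 20% | 91.2% | 94.9% | 93.6% |
| 6 | 0 | 89.9% | 89.1% | 85.8% |
| 6 | 10% | 90.5% | 92.1% | 89.3% |
| 6 | 20% | 90.8% | 94.8% | 92.4% |

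Changing both gains about 1 to 2 points at a 10% share and about 4 at 20%, and costs about 1 point or less when centre variance is nil. Adding the term alone costs about 1 to 4 points when centre variance is nil.

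**5. Validity.** In a separate simulation without a centre term (3 or 5 centres, share 0 to 20%), the mean error was within 0.01 SD and type I error lay between 0.043 and 0.054.

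**The case against.** Stratifying a 56-patient trial on one prognostic factor is a legitimate choice, and the test remains valid. That stands. A reader might infer a biased treatment effect or an inflated false-positive rate. Step 5 shows neither: the issue is chance imbalance in the one realised allocation, plus precision.

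The planned analyses already blunt the problem. The group-by-time contrast and the T0 covariate remove or reduce stable centre differences, such as case mix or a consistent habit in timing the test. That also stands. It leaves differences in change, and it means that the variance shares in steps 3 and 4, set without T0 adjustment, may be generous for the adjusted analysis. No document supports a particular share.

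A reader might also infer that a single freezing-stratified list will be cut into runs of envelopes and shared among sites. The article does not say how envelopes reach the centres or what blocking is used, and such detail is commonly left to the full protocol. The point does not depend on it, since the article does state its stratification factor and its model terms.

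Finally, centre-by-freezing cells would be small: six centres give 12 cells, or fewer than 5 patients each (56/12 = 4.7), so blocks stay incomplete. The simulation used incomplete blocks and the gain survived. Many very small centres would still call for a different allocation method.

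**Conclusion.** The concern holds as a modest design weakness resting on choices the article states: a multicentre trial with differing centres, freezing of gait as the only stratum, and models limited to time, group and T0. With 4 to 6 equal centres, a split of about 10:4 or worse in some centre has a probability of roughly one third to one half; with 3 centres it is about 8%. The gain from correcting this is about 1 to 4 points of power if centre carries 10 to 20% of the variance, against a cost of about 1 point or less if it carries none. The number and size of centres and the variance share are all assumptions. The documents do not support calling the primary test invalid or the trial underpowered on this ground. The case for acting is that the remedy is cheap and the allocation cannot be changed afterwards.

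**What to change.** **Allocation.** Balance on centre as well as freezing of gait. If centres are few, the remote investigator who already generates the sequence produces a separate list per centre within the freezing strata, with randomly varied block sizes not disclosed to sites, and envelopes are numbered per centre. If centres are many or small, use central allocation that balances the two factors jointly.

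**Analysis.** Include centre and freezing of gait in both the split-plot ANOVA and the T0-adjusted ANCOVA of the Timed Up and Go. In the split-plot model both need their interaction with time, or they do not bear on the group-by-time contrast. Pool very small centres by a rule set before unblinding.

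Make the two changes together, because a centre term without balanced allocation loses about 1 to 4 points of power if centre variance is nil.

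**Cost.** New lists from the same online generator and extra model terms. The downside is a few degrees of freedom and some small strata. No extra patients, visits or staff are needed.
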